## Abstract

**Background:**

Increasing levels of insecticide resistance as well as outdoor, residual transmission of malaria threaten the efficacy of existing vector control tools used against malaria mosquitoes. The development of odour-baited mosquito traps has led to the possibility of controlling malaria through mass trapping of malaria vectors. Through daily removal trapping against a background of continued bed net use it is anticipated that vector populations could be suppressed to a level where continued transmission of malaria will no longer be possible.

**Methods/design:**

A stepped wedge cluster-randomised trial design was used for the implementation of mass mosquito trapping on Rusinga Island, western Kenya (the SolarMal project). Over the course of 2 years (2013–2015) all households on the island were provided with a solar-powered mosquito trapping system. A continuous health and demographic surveillance system combined with parasitological surveys three times a year, successive rounds of mosquito monitoring and regular sociological studies allowed measurement of intervention outcomes before, during and at completion of the rollout of traps. Data collection continued after achieving mass coverage with traps in order to estimate the longer term effectiveness of this novel intervention. Solar energy was exploited to provide electric light and mobile phone charging for each household, and the impacts of these immediate tangible benefits upon acceptability of and adherence to the use of the intervention are being measured.

**Discussion:**

This study will be the first to evaluate whether the principle of solar-powered mass mosquito trapping could be an effective tool for elimination of malaria. If proven to be effective, this novel approach to malaria control would be a valuable addition to the existing strategies of long-lasting insecticide-treated nets and case management. Sociological studies provide a knowledge base for understanding the usage of this novel tool.

**Trial registration:**

Trialregister.nl: NTR3496 – SolarMal. Registered on 20 June 2012.

**Electronic supplementary material:**

The online version of this article (doi:10.1186/s13063-016-1469-z) contains supplementary material, which is available to authorized users.

## Background

Significant reductions in malaria infections and mortality since the year 2000 are associated with increased coverage of vector control interventions such as long-lasting insecticidal nets (LLINs) and indoor residual spraying (IRS), as well as improved availability and access to preventive therapies, diagnosis and treatment [1]. However, the development and spread of insecticide resistance and the occurrence of residual malaria transmission outdoors and in the early evening threaten the long-term sustainability of current tools for malaria vector control. This necessitates the development of new alternatives, particularly as many regions move towards malaria elimination [2, 3]. In 2013 an estimated 538,000 people lost their lives due to malaria with 90 % of those deaths occurring in the WHO African Region [4]; a region where millions of dollars of malaria-associated economic losses are suffered every year [5]. With the addition of new tools for malaria control that could reduce household spending on malaria-associated expenses, millions of people could potentially escape the cycle of poverty and disease. Estimates show that for each dollar spent to control malaria, up to 60 USD worth of benefits could be gained for the overall well-being of a society in the sub-Saharan Africa region [6].

Studies to characterise the components of human odour which are attractive to host-seeking *Anopheles gambiae s.s.* have led to the identification of a large number of compounds [7–9] which, at appropriate concentrations, can be combined to create synthetic mosquito lures that mimic a human host [8, 10]. These lures can remain attractive to mosquitoes even after a year of use [11]. Synthetic lures can be placed in counterflow trapping systems and used to lure and capture host-seeking mosquitoes both inside and outside houses [12–14]. By capturing mosquitoes outdoors, rates of mosquito house entry can be lowered by between 33–80 % under semi-field conditions [10, 13] and by 50 % in the field [15]. It is anticipated that above a certain threshold level of trap coverage, traps could be used to effectively reduce *Anopheles gambiae s.l.* and *Anopheles funestus* populations enough to lower the entomological inoculation rate (EIR) to a level at which malaria transmission cannot be sustained [16]. The principle of mass trapping for the control of tsetse flies has already been demonstrated in several African countries [17, 18], and we expect that this principle can also be applied to malaria vectors.

The Asembo Bay area of western Kenya was one of the first regions in sub-Saharan Africa to receive insecticide-treated bed nets (ITNs) as part of a trial in the mid-1990s [19–21], but despite increasing population coverage of ITNs since 2000, as well as provision of artemether-lumefantrine, intermittent IRS and presumptive treatment in pregnancy, malaria remains prevalent in western Kenya [22, 23]. The history of sustained vector control interventions as well as extensive prior understanding of malaria and malaria interventions in the Lake Victoria region of Kenya mean that this setting is ideal for a study investigating the efficacy of odour-baited traps combined with LLINs and case management for malaria control.

In this rural region of Kenya, few residential buildings are connected to the main electrical grid, and most households light their homes using kerosene tin lamps. The requirement of electrical energy to power the fan inside the odour-baited trap prompted the decision to integrate the mosquito trapping systems into a solar-home system, henceforth referred to as a solar-powered mosquito trapping system (SMoTS). The SMoTS includes two light emitting diode (LED) lights and a mobile phone charging port in addition to the odour-baited mosquito trap. These additional, immediate, private benefits of the system were expected to increase usability and improve adherence to the public health intervention, which requires the sustained participation of residents [24].

Here we describe the study design and methods used by the SolarMal project to test this intervention on Rusinga Island, western Kenya (the WHO Trial Registration Data Set is given in Additional file 1, and a protocol checklist is given in Additional file 2). The SolarMal project is the first trial to measure the efficacy of this novel approach to malaria vector control. A stepped wedge cluster-randomised approach was applied to the intervention rollout so that the intervention coverage gradually increased from no coverage to coverage of all eligible households over the course of 24 months. During the course of this study we aimed to determine whether the addition of daily removal trapping of malaria mosquitoes to the Kenyan national malaria control strategy (LLINs plus case management) will lead to elimination of malaria from Rusinga Island, western Kenya.

### Study objectives

#### Primary objective

The primary objective is to measure the effect of mass mosquito trapping on clinical malaria incidence, measured as fever plus positive rapid diagnostic test (RDT) result.

#### Secondary objectives

The medical objectives are as follows (all outcome measures include contemporaneous comparison of intervened with non-intervened areas, as well as before-and-after measures of intervened areas compared with baseline):To determine the impact of mass mosquito trapping on malaria prevalence measured by RDT, with subsequent high-resolution melting PCR used to estimate the prevalence of sub-patent malariaTo calculate differences in both measured and reported all-cause fevers following the introduction of odour-baited traps

The entomological objectives are as follows (all outcome measures include contemporaneous comparison of intervened with non-intervened areas, as well as before-and-after measures of intervened areas compared with baseline):To assess whether the mass trapping of mosquitoes reduces the population density of malaria vectors on Rusinga IslandTo determine whether the mass distribution of odour-baited mosquito traps leads to changes in mosquito species compositionTo record changes in entomological inoculation rate associated with implementation of the interventionTo compare mosquito densities and species composition indoors and outdoors

The sociological objectives are as follows:To determine the behavioural, socio-cultural and organisational factors that influence the effective and sustainable use of SMoTSTo foster learning relevant to adapting the implementation and sustainability strategy as an integral component of the interventionTo understand how the introduction and use of SMoTS affects and/or is affected by the use of other malaria control interventions

## Methods/design

### Study area and participant eligibility

The study took place on Rusinga Island, western Kenya, an island that is located approximately 75 km southwest of the city of Kisumu and has a surface area of around 44 km^2^. Research activities are conducted through the Thomas Odhiambo Campus of the International Centre of Insect Physiology and Ecology (*icipe*) in Mbita Point, located 2 km from Rusinga Island. In a population census conducted by the project in May 2012, the total population of the island was 23,337 people, living in 4062 households [25]. The majority of the population belongs to the Luo ethnic group, and Dholuo is the main language spoken by residents. A household (locally referred to as a homestead or *dala*) may comprise more than one house. The primary occupations of people are fishing in Lake Victoria and small-scale farming. The climate is tropical with a long rainy season typically occurring from February to May with a shorter rainy season from October to November. Malaria is typically endemic in this region, and transmission occurs throughout the year [22, 26].

All households and residents of Rusinga Island were eligible for inclusion in the study with recruitment commencing in June 2012 and continuing until November 2015 (Figs. 1 and 2). The assignment of households to clusters and metaclusters (see the section on study design below) was completed in May 2013, and any household constructed before this point was eligible to receive an odour-baited trapping system. Households constructed after this time were eligible to participate in the health and demographic surveillance, parasitological, entomological and sociological studies, but were no longer eligible to receive a SMoTS. As the rollout of SMoTS took two years to complete and we did not return to previously installed project clusters to install SMoTS in new households, limiting SMoTS to those households already built at the start of the rollout meant that the intervention coverage levels were consistent across the island. Had SMoTS been installed in all households (including those built after the start of the rollout) there would have been a greater coverage of SMoTS in those clusters which received the intervention later in the two year rollout process.

**Fig. 1 Fig1:**
[figure not shown]
SPIRIT flowchart for the SolarMal project showing the timing of enrolment, interventions and assessments

**Fig. 2 Fig2:**
[figure not shown]
Diagram showing the workflow of the SolarMal project from planning stages to completion of intervention rollout

In order for the results of the intervention to be generalisable across whole societies, all residents of the island were eligible for participation, regardless of age, gender, ethnicity, health status or whether they were natives of the island. For overall participation in the study and recruitment to health and demographic surveillance (HDSS) as well as malaria testing by RDT, individual written consent was provided by adults aged 18 years and older for themselves and for mature minors. For persons aged 13–17 years, individual assent was provided alongside written consent of an adult. For persons under 13 years of age, written parental consent was provided before recruitment to the study. All consent forms were in either English or Dholuo and were signed by the recruiter (a member of the project staff) and a witness. Informed verbal consent was provided by individuals or heads of household before participation in sociological and entomological studies, respectively. Participation in the study was voluntary, and all participants were free to withdraw at any time without giving a reason for their withdrawal. Unique identification numbers were assigned to preserve the anonymity of study participants.

Enumeration of the population and recruitment of participants were ongoing throughout the study period (i.e. from May 2012 until November 2015). Three rounds of HDSS took place during each year of the study, with recording of births and deaths as well as in- and out-migration across both arms of the study. A unique identification number was assigned to every individual, house and household recruited to the study during the HDSS.

The population of Rusinga was sensitised about project activities and findings in a number of ways throughout the course of the study. An initial community launch day was held on the island in August 2012 with the aim of informing community members about the project using song, dance, sketches and speeches. In order to ensure good communication between the project scientific staff and the study participants, a community advisory board (CAB) was established, including representatives of key groups of stakeholders. The CAB met formally four times each year to receive updates on project progress and plans from scientific staff and in turn to provide feedback from the community and to discuss project plans. Informal meetings between the CAB and project staff were also held whenever the need arose. In May 2013 a public balloting event was held where the sequence of the rollout was selected with the participation of community members [24]. Thereafter, weekly community training workshops were held to train each cluster of approximately 50 households in the maintenance of SMoTS.

### Intervention: solar-powered mosquito trapping systems (SMoTS)

The odour-baited traps (Suna traps) that were used during this intervention were developed in collaboration between Wageningen University and Research Centre (the Netherlands), the International Centre of Insect Physiology and Ecology (*icipe*, Kenya) and Biogents AG (Germany) [13]. The traps were baited with a blend of five organic attractants that mimic a human odour and lure mosquitoes towards the trap [10]. The blend of five chemicals was supplemented with a carbon dioxide mimic [27] in order to increase the attraction of malaria vectors to the trap. The odour baits were produced at the field site in Kenya by impregnating strips of nylon with each attractant at the appropriate concentration [28]. Baits were prepared in batches and stored at –20 °C to prevent the organic chemicals from volatising before use. Semi-field studies have shown that baits remain attractive to *An. gambiae* even after weekly use over 52 weeks [11]. During the course of the study odour baits were replaced in each intervened household by project field staff at 3-monthly intervals.

Previous studies have shown that a host-seeking mosquito can detect human or animal odours at distances of 50 m or more [29, 30], and we expect that the odour-baited Suna trap has a similar radius of attraction. Traps were suspended outside houses, beside the primary sleeping area with the fan section at 30 cm above the ground, a position that has previously been shown to result in the highest mosquito catch rates [13]. As described in the preceding background section, the requirement of electrical power for the trap meant that each SMoTS comprised an odour-baited mosquito trap, solar panel, battery, two LED lights, one mobile phone charging port and the associated electrical wiring.

During the course of the study each eligible household on Rusinga Island was offered one SMoTS. If a household comprised more than one residential structure (house), the project staff requested household members to reach a consensus agreement as to which house should have the SMoTS installed. If no consensus was reached, the SMoTS was not installed.

Two weeks prior to SMoTS installation in any given cluster, residents of the cluster were invited to attend a community training workshop held at a local community centre, such as a church or school building. During each training workshop study participants were reminded of the aims of the study and took part in question-and-answer sessions about malaria transmission and prevention. Demonstration SMoTS were used to show participants how the system operates and how to empty the trap of mosquitoes and clean it on a weekly basis [31]. Contact information for project-employed technicians was provided so that any technical faults in the systems could be reported and resolved promptly.

### Study design

The SolarMal trial used a stepped wedge cluster-randomised trial (SWCRT) design [32] where the intervention is allocated to geographically defined clusters in a randomised order until full coverage is achieved. This trial design is appropriate for a vector control intervention such as an odour-baited trap which is expected to have an impact that extends to an area beyond the house on which it is installed (spill-over effect). Replication of the intervention in multiple clusters while maintaining contemporaneous control areas can be achieved with a cluster-randomised trial (CRT) design, typically aiming to reduce infection at the individual level by targeting a whole community/area with the intervention. The stepped wedge design provides the opportunity of attaining area-wide coverage and group randomisation by the gradual crossover of all clusters to the intervention arm. In this way the effect of the intervention can be measured when used at a relatively small scale, up to mass coverage. Given the contemporaneous controls, the stepped wedge design also allows some ability to control for time.

### Randomising the intervention allocation

Clusters of households were constructed by means of a travelling salesman algorithm whereby the shortest distance from one household to another was continually chosen, creating a cluster after every 50 or 51 households (see Fig. 3). The number of houses per cluster is expected to be large enough for measurement of the maximal intervention effect at the centre of the cluster, avoiding spill-over of mosquitoes from surrounding non-intervened areas resulting in sustained malaria transmission. The degree of protection among people living in households at the edges of clusters may be affected by mosquitoes from surrounding non-intervened areas; alternatively, intervened households located at cluster edges may exert an effect on mosquitoes in neighbouring areas which are yet to receive the intervention, as was observed during the early bed net studies [21]. Our clusters were expected to be large enough to include both substantial areas at the centre where the maximal intervention effect is obtained, and peripheral areas where spill-over of mosquitoes from surrounding non-intervened areas could be measured.

**Fig. 3 Fig3:**
[figure not shown]
Rusinga Island with 81 project clusters, each containing 50–51 households, numbered consecutively in the order in which the SMoTS were installed. Metaclusters, each containing nine clusters, are outlined in *bold red lines*. Insets show close-up views of geographically smaller clusters in the northwest and southeast of the island. The blank space at the centre of the island is an uninhabited hill

Computer simulations of possible rollout scenarios were made on the basis of a human susceptible-infected-susceptible transmission model [33]. A hierarchical design was selected and adopted as the rollout strategy for SolarMal. The design groups the 81 clusters of 50 or 51 households into nine larger areas, each referred to as a metacluster. Within every metacluster the intervention was subsequently introduced to each of nine clusters in a random order. Once the intervention had been applied to all clusters in one metacluster, the rollout moved randomly to the next metacluster; all clusters eventually received the intervention according to this SWCRT design. The nature of the intervention (visible trap outside the house and solar panel on the roof) meant that it was not possible to blind the intervention.

Prior to a community rollout ballot held in May 2013, a large number of possible rollout sequences were computer generated, each consisting of a distinct ordering of the 81 clusters [33]. Nine possible rollout sequences (each of which was compliant with statistical power calculations and requirements of the community) were presented by the researchers for blind selection by community members, with one sequence starting in each of the nine metaclusters and preserving independence among metaclusters. After placing a printed map of each sequence in a sealed, unmarked envelope and placing the nine envelopes into a box, one member of the community was chosen at random to draw an envelope and open it to reveal the order of the rollout which would be followed [24]. The selected SWCRT sequence is illustrated in Fig. 3.

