### Analytical plan

The datasets included for the analysis comprise results of the HDSS, clinical malaria surveys, cross-sectional malaria prevalence surveys and monitoring of mosquito densities. Malaria fever incidence is the primary outcome of the trial. Data are included up to the end of the next month after full intervention coverage was attained. For analyses of parasitological as well as entomological outcomes, intervention status is classified week by week on the basis of whether traps had been installed in the cluster. The whole study cluster is classified as intervened or non-intervened based on whether installation was complete in that cluster by the end of the week. Clusters are excluded from analysis during weeks in which some, but not all, of the households were provided with the intervention (i.e. during the week in which installations took place in that cluster). For malaria prevalence and incidence, the numbers and proportions of positive RDT tests were summarised by week and arm of the trial. For mosquito densities, rates of anophelines collected per trapping night were presented by week and arm of the trial.

Following the SWCRT design described by Silkey et al. [33], an analytical plan was constructed. The primary analysis of the impact of the trial on clinical malaria incidence, prevalence and vector densities follows two measures of effect: a contemporaneous comparison comparing the outcomes in intervened clusters with the not yet intervened clusters and a comparison of the final results in intervened areas with the baseline status. Generalized linear mixed models (GLMMs) with a binomial distribution will be deployed to carry out significance testing against the null hypothesis of no effect using a likelihood ratio test. For mosquito densities a GLMM will be used with a Poisson distribution. For analysis of medical and entomological data, random effects will be used to allow for spatial effects (cluster) as well as effects of round of surveillance (time period within cluster). Final models will consider possible confounding effects on the relationship between the intervention effect and measured outcomes. The analytical plan did not include any interim analyses.

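### The rollout was ordered metacluster by metacluster, but the planned mixed models have no random effect above cluster level, so the test of the contemporaneous comparison is anti-conservative if clusters in a metacluster are correlated

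*Protocol article*

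**What the plan says.** All of this is in the Protocol article.

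- **Randomising the intervention allocation**, on the structure: "The design groups the 81 clusters of 50 or 51 households into nine larger areas, each referred to as a metacluster". On the order inside a metacluster: "Within every metacluster the intervention was subsequently introduced to each of nine clusters in a random order". On the order of metaclusters: "Once the intervention had been applied to all clusters in one metacluster, the rollout moved randomly to the next metacluster".
- The same section says that nine candidate sequences went into the ballot, "with one sequence starting in each of the nine metaclusters and preserving independence among metaclusters", and that one was drawn.
- **Analytical plan**, on exposure: "intervention status is classified week by week on the basis of whether traps had been installed in the cluster".
- **Analytical plan**, on the model: "random effects will be used to allow for spatial effects (cluster) as well as effects of round of surveillance (time period within cluster"). The models are used to "carry out significance testing against the null hypothesis of no effect using a likelihood ratio test".

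No metacluster term, fixed or random, is named. The remark that final models will consider confounders concerns covariates, not the correlation structure.

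**The concern.** A level that governed the order of treatment is absent from the model that supplies the p-value. Because each metacluster is finished before the next begins, at most one metacluster is partly covered at any date. At the midpoint about 81/2 = 40.5 clusters are covered, which is 4.5 metaclusters against 4.5. Comparisons inside a metacluster are brief: 24 months / 9 is about 2.7 months per metacluster, against 4 months between surveillance rounds at three rounds a year.

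The period-within-cluster effect does not help. It sits below cluster level and is independent from one cluster to the next. Variation shared by the nine clusters of a metacluster is therefore averaged in the model as if over 81 units, when it averages over nine. If such variation exists, the false-positive risk falls on the primary outcome and on prevalence.

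**Working it through.** **Nothing to reproduce.** The article gives no type I error, intracluster correlation (ICC) or metacluster variance, so every variance component below is an assumption.

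**Method.** Take cluster-by-round means with fixed round effects (assumed; the section does not state them). Let between-cluster variance be σ², a fraction ρ of it permanent, so a = σ²ρ and b = σ²(1−ρ). Let e be the sampling variance and R the number of rounds.

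- Working covariance, as planned: V0 = I81 ⊗ (aJ + (b+e)I).
- True covariance when a share s is common to the metacluster: V1 = [(1−s)I81 + s(I9 ⊗ J9)] ⊗ (aJ + bI) + eI.
- Estimator: L = (X′V0⁻¹X)⁻¹X′V0⁻¹.
- Model variance: the treatment entry of (X′V0⁻¹X)⁻¹. True variance: the treatment entry of L V1 L′.
- Type I error = 2Φ(−1.96 × model SE / true SE).

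The rollout is spread evenly over R = 6 rounds in random hierarchical order, with status taken at mid-round.

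**Prevalence.** Inputs from the article: p = 0.237; 907 persons, or 10 % of 23,337 = 2,334, per round. Assumed: ICC 0.02–0.10 and ρ 0.5–0.8. Then σ² = ICC·p(1−p) and e = (1−ICC)·p(1−p)/(n/81).

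| Share s | True SE / model SE | Type I error |
|---|---|---|
| 10 % | 1.08–1.20 | 7–10 % |
| 25 % | 1.18–1.44 | 10–17 % |
| 50 % | 1.34–1.77 | 14–27 % |

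The ends of these ranges move by about a point with the way the order is mapped on to rounds, hence roughly 6–26 % overall.

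**Clinical incidence.** Persons per cluster-round: 7,914/81 ≈ 98 or 23,337/81 ≈ 288. The baseline rate is not stated. The power statement (80 % power, 52 % reduction, 7,914 persons) implies about 1.1 % if 7,914 is the total and about 0.54 % if it is per arm; 0.5–1.1 % is used. Assumed between-cluster coefficient of variation (CV) 0.15–0.4 and ρ 0.5–0.8.

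| Share s | CV 0.15–0.25 | CV 0.4 |
|---|---|---|
| 10 % | 5–7 % | 6–8 % |
| 25 % | 5.5–10 % | 8–12 % |
| 50 % | 6–15 % | 10–19 % |

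With CV up to 0.7, incidence 0.5–2 %, 288 persons and eight rounds, type I error reaches 26 % at a 50 % share. The result is sensitive to between-cluster variation that the article does not report.

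**Where the inflation comes from.** A separate calculation used nine rounds, cluster SD 0.3 and cluster-by-period SD 0.5, with 1,500 simulated trials per row analysed by likelihood ratio test.

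| Metacluster SD | Metacluster-by-period SD | SE ratio | Type I, analytic | Type I, simulated | 95 % interval covers |
|---|---|---|---|---|---|
| 0 | 0 | 1.00 | 5.0 % | 5.5 % | 95 % |
| 0.4 | 0 | 1.11 | 7.6 % | 8.3 % | 92 % |
| 0.4 | 0.1 | 1.21 | 10.6 % | 11.0 % | 89 % |
| 0.4 | 0.2 | 1.45 | 17.8 % | 16.6 % | 82 % |
| 0.4 | 0.3 | 1.71 | 25.2 % | 27.1 % | 75 % |

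A constant difference between metaclusters does limited harm, because every cluster crosses over and is partly its own control. Shared time trends do most of it.

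**Control case.** With the 81 clusters ordered freely across the island, the same planned model stays near 5 % (analytic 4.9–5.5 %). The problem comes from the hierarchical order combined with the missing level.

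**The case against.** The strongest reply is that inflation is not shown. It needs positive correlation within metaclusters beyond the cluster and cluster-period terms, and the article reports none. That stands: the claim is conditional. Plausibility comes from the article itself, which builds clusters by proximity, groups them into larger areas, expects mosquitoes and trap effects to cross cluster borders, and lists vegetation and wetness as environmental confounders.

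A second reply is that the article is condensed and cites a separate design paper, so a fuller plan may contain a metacluster term. That is possible. However, the Analytical plan names its random effects, so this is a stated specification and not merely an omitted detail.

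Stronger readings that a reader might draw are not supported:

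- *That the model has a cluster effect and nothing else.* It also has time period within cluster. The accurate statement is that nothing lies above cluster.
- *That the test certainly exceeds 5 %.* With no metacluster variance it holds 5 %.
- *That the prevalence figures carry over to the primary outcome.* Clinical malaria is rarer, sampling error is a larger part of the variance, and the inflation is generally smaller.
- *That mosquito densities and the final-versus-baseline comparison are affected to the same extent.* Neither was computed. The first uses 80 households per round under a Poisson model; the second compares the same areas before and after.

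**Conclusion.** The point holds in conditional form. The rollout has two levels, the stated models have nothing at the upper one, and the 81 clusters are treated as independent of each other. If clusters in a metacluster are positively correlated, the likelihood ratio test of the contemporaneous comparison is anti-conservative and its intervals too short.

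The size rests on assumption: roughly 6–26 % type I error for prevalence and 6–19 % for clinical incidence at metacluster shares of 10–50 %. It is close to 5 % where the share or the between-cluster variation is low. Direction is secure given positive correlation; magnitude is not. This should be fixed before the results are interpreted, but it does not invalidate the design.

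**What to change.** Add random effects for metacluster and for metacluster by round to the mixed models for the contemporaneous comparison, keeping the two planned effects. As only nine metaclusters inform the new components, apply a small-sample correction, for example a parametric bootstrap of the likelihood ratio statistic.

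As a sensitivity analysis only, run a permutation test over the full set of admissible computer-generated hierarchical sequences. Document the admissibility rules and justify this reference set, because the physical draw was one of nine sequences. A test confined to those nine cannot give a p-value below 1/9, about 0.11.

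**Cost.** The rollout is complete, so only the analysis changes. In the four scenarios above with metacluster variance, the SE from the fuller model is 1.02, 1.13, 1.33 and 1.46 times the one that the planned model would report; with no such variance the ratio is 1.00. The fuller model is also more efficient than the planned estimator really is (last scenario: SE 0.1126 against a true 0.1317). The permutation set must be rebuilt, which is more than a wording change.
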